### Recruitment

Patient inclusion started in May 2022 in eight Japanese hospitals. Enrollment in ongoing.

### Assigning interventions

#### Allocation

Randomization is centralized, web-based, and accessible 24 h a day; it is balanced (1:1) and stratified by center and the cause of the indication for ERCP [for bile duct cannulation or otherwise (for pancreatic duct and both bile and pancreatic ducts cannulation)].

#### Sequence generation

The randomization sequence is generated by a professional technician from Hyogo University who is not involved in patient recruitment. The sequences are implemented using the software used for data collection.

#### Blinding

The allocation result is unknown to the patient because knowing it may affect the appearance of abdominal pain, which predicts the onset of PEP.

### Data collection, management, and analysis

#### Data collection and management

The study data are recorded in an electronic web-based case report form (eCRF) from the medical records of each patient (source data) by the trial site personnel. The data manager, in cooperation with the coordinating investigator, established the trial database by exporting data from the eCRF. Any protocol deviations are recorded in either the eCRF or the medical records.

#### Statistical analysis

The full analysis set (FAS) is the population of patients enrolled in the study, excluding duplicate or erroneous enrollments, cases of inadequate study treatment, and cases in which no post-assignment data are available.

The per-protocol set (PPS) excludes FAS cases in which efficacy could not be assessed due to inadequate observation, etc., and cases of serious deviation from or violation of the study protocol.

For each allocation group, the percentage of PEP occurrences will be calculated using the number of FAS cases as the denominator. The exact 95% confidence intervals (CI) of Clopper and Pearson will be calculated. The frequencies, expression proportions, and 95% CI will also be calculated for each group. Fisher's exact test will be used to compare the groups. The test will be two-tailed with a significance level of 5%. The same analysis will be performed for PPS as a reference.

After dividing the patients into subgroups according to background factors, comparisons between the groups will be made. Binary data (PEP and other comorbidities) will be evaluated using odds ratios and 95% CI, and compared using Fisher's exact test. When the background factor is a continuous variable, subgroups will be created based on the median value. The results of the subgroup analysis will be graphically represented by a forest plot.

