### Interventions

A diagram of the study protocol is shown in Fig. 2. All patients are fasted on the day of ERCP. NSAIDs suppositories are not administered. During the examination, the heart rate, non-invasive blood pressure, and oxygen saturation are monitored, and pain is reduced using sedatives and analgesics.

The patients are randomized into the ice water or control group prior to ERCP.

ERCP is performed using a side-viewing duodenoscope (TJF-260 V or TJF-Q290V; Olympus Medical Systems Co. Ltd., Tokyo, Japan) in a standard manner.

In the ice water group, a total of 250 mL of ice water is injected, which is done in five increments using a 50 mL syringe, toward the papilla at the end of ERCP. Duodenal fluid is aspirated after each 50-mL injection of ice water, and the injection is repeated.

During ERCP, the total examination time (from insertion of the scope to its removal), procedure time (from the start of cannulation to the end of treatment), time required for cannulation, and the number of papillary contacts, etc. are recorded on the findings form (Fig. 3).

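### The primary analysis set drops patients after randomisation for inadequate study treatment, an exclusion that falls mainly on the ice water arm and opens the comparison to selection bias

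*Protocol article*

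**What the plan says.** Under Statistical analysis, the FAS is the enrolled population "excluding duplicate or erroneous enrollments, cases of inadequate study treatment, and cases in which no post-assignment data are available". It governs the primary result, because "the percentage of PEP occurrences will be calculated using the number of FAS cases as the denominator". The arms are compared by a two-sided Fisher's exact test at the 5% level.

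The PPS is taken from the FAS by removing patients whose efficacy could not be assessed and "cases of serious deviation from or violation of the study protocol". Its role is secondary: "The same analysis will be performed for PPS as a reference".

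Under Interventions, "The patients are randomized into the ice water or control group prior to ERCP". The study treatment is then described for one group: "In the ice water group, a total of 250 mL of ice water is injected", in five 50 mL portions, "toward the papilla at the end of ERCP". No injection, sham or otherwise, is described for controls. Under Blinding, only the patient is said to be unaware of the allocation. The article does not define inadequate study treatment or say who judges it.

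**The concern.** Randomisation makes the arms comparable at the moment of allocation. Here the primary set is settled later, by whether study treatment was adequate, and that is known only once the ERCP is over. A shortfall in the injection can remove an ice water patient. A control patient whose procedure went the same way has no injection to fall short and would ordinarily stay in.

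If injections are cut short or omitted after difficult procedures, the patients removed would tend to be at higher risk: difficult cannulation is among the PEP risk factors listed under Definitions. Removing them from one arm lowers that arm's PEP rate with no treatment effect. Because the term is undefined and only the patient is stated to be blinded, the judgement could also be made with knowledge of the allocation, and possibly of the outcome.

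At stake is whether the main result of a superiority trial compares the groups as randomised. An unseen analysis plan could restore that comparison as primary only by contradicting the FAS definition given here.

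**Working it through.** **1. The plan's own figure.** Inputs from Sample size: PEP 10% against 5%, two-sided α 0.05, power 0.80. With pooled variance and no continuity correction:

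n = [1.960·√(2·0.075·0.925) + 0.842·√(0.10·0.90 + 0.05·0.95)]² / 0.05² = (0.730 + 0.312)² / 0.0025 ≈ 434.4, so 435 per arm.

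This matches the stated 435. The sample size calculation is not in question on this point.

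**2. Effect of a one-arm exclusion when ice water does nothing.** Assume 440 patients per arm (the planned enrolment) and a true PEP risk of 10% in each arm as randomised. Let f be the share of the ice water arm excluded and r the PEP risk of those excluded. Both are assumptions; the article gives neither. No control patient is excluded in this calculation, which is also an assumption.

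Rate left in the analysed ice water arm = (0.10 − f·r) / (1 − f).

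Example, f = 0.05 and r = 0.30: (0.10 − 0.015) / 0.95 = 8.95%, in 418 patients.

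The probability of a significant result in each direction was computed exactly for Fisher's two-sided test against 440 controls at 10%:

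| Excluded f | Risk r | Ice water n | Analysed ice water rate | Spurious difference (points) | False benefit | False harm |
|---|---|---|---|---|---|---|
| 0 | – | 440 | 10.0% | 0 | 1.9% | 1.9% |
| 1% | 30% | 436 | 9.8% | 0.2 | 2.7% | 1.8% |
| 5% | 20% | 418 | 9.5% | 0.5 | 3.8% | 1.2% |
| 5% | 30% | 418 | 8.95% | 1.1 | 6.6% | 0.6% |
| 8% | 30% | 405 | 8.3% | 1.7 | 12.4% | 0.2% |
| 5% | 10% | 418 | 10.0% | 0 | 2.1% | 2.2% |
| 10% | 5% | 396 | 10.6% | −0.6 | 1.1% | 4.0% |

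The nominal error in each direction is 2.5%. The row with r = 10% shows exclusions unrelated to risk: there is no bias, and the small change from 1.9% comes from the discreteness of Fisher's test. The bias favours ice water only when r exceeds 10%, and reverses below it.

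**3. Cost of keeping everyone.** Suppose the PEP rate is 5% among adequately treated ice water patients. The rate in the whole arm is then (1 − f)·0.05 + f·r.

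- f = 5%, r = 10%: 5.25%. Fisher power is 72% for all randomised patients, against 79% for the FAS as written.
- f = 10%, r = 20%: 6.5%. Power is 43%, against 77%.

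**The case against.** The strongest reply is that the article does not confine inadequate study treatment to one arm or equate it with less than 250 mL. It could cover a failed or abandoned ERCP, which occurs in both arms, or a control patient given ice water. A reader might infer that the exclusion can arise only in the ice water arm; the text does not support that. It supports only that the exclusion falls mainly there, because no injection is described for controls.

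A reader might also infer that the comparison is biased in favour of ice water. That is plausible but not established. If the excluded patients are at low risk, for example because the papilla was never reached, the bias runs the other way. Exclusion criterion 4, which removes predicted inaccessibility before randomisation, makes that source less common. If exclusion is unrelated to risk, there is no bias.

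The size is also open. The plan's allowance for losses is 5 of 440 per arm (1.1%), although the reasons listed for it do not include inadequate treatment. At 1% excluded the effect is small even at 30% risk. Nor does it follow that a positive result could not be credited to ice water: a clear result with few exclusions, reported by arm, would remain interpretable.

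These points limit the claim about direction and size. They do not remove the defect. Even if applied in both arms, an undefined exclusion made after randomisation does not belong in the primary set of a superiority trial.

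**Conclusion.** The point holds as a matter of design. The primary set removes patients for a reason that arises after randomisation, depends on treatment received and falls mainly on the ice water arm. No analysis of all randomised patients is named alongside it. The primary comparison is open to selection bias, plausibly towards ice water if injections are curtailed after difficult procedures, but the document settles neither direction nor size.

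In the scenarios above, the chance of a false benefit runs from 1.1% to 12.4%, against 1.9% with no exclusion, and the spurious difference from −0.6 to 1.7 points, against a planned effect of 5 points. These figures rest on assumed exclusion rates and risks, on exclusions in the ice water arm alone, and on 10% PEP in both arms. They show what the rule permits and do not forecast what will happen. Because the rule governs the primary result, it should be changed before outcomes are compared by arm.

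**What to change.** Define the FAS as all randomised patients, analysed in the arm to which they were allocated. Exclude only duplicate or erroneous registrations, judged on pre-randomisation data without regard to allocation or outcome, and patients who withdraw consent to use of their data. Move inadequate study treatment to the PPS exclusions, which already cover serious deviations.

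Patients with no post-assignment data then need a stated rule. Report their number by arm and cover them with a simple sensitivity analysis, for example counting them all as PEP and then all as no PEP.

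The change takes a few sentences in the analysis section, needs no new procedures, and leaves the calculated 435 and the target of 440 per arm as they are. The downside is dilution: the estimate shrinks in proportion to the share of ice water patients not adequately treated. That is modest if such cases are rare but could be more than slight if they are frequent, as the fall in power to 43% in the working shows. The higher power of the FAS as written is no reason to keep it, because part of its contrast can come from the exclusion itself. The PPS remains available for the effect in adequately treated patients.

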### Sample size

#### Number of patients

Without any form of prophylaxis, the incidence of PEP in the native papilla can reach 10–15% as reported in previous studies[1, 11, 18, 19]. Our previous study revealed that ice water injection reduced the incidence of PEP from 11 to 4%, and the relative risk reduction was 63.6%[14]. Assuming a baseline PEP risk of 10% in normal native papilla, a two-sided α = 0.05 and a power of 0.8, 435 patients per study arm are required to detect a 50% reduction in the incidence of PEP to 5%. This absolute reduction in incidence is believed to be clinically relevant and substantial enough to change the existing clinical practice. We aim to enroll 440 patients into each group to accommodate patients who will be lost to follow-up, missing data, or withdrawal of consent.

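### The primary test is a crude Fisher's exact test that leaves out the randomisation strata, has about 77.7% power rather than the stated 80%, and comes with no overall effect estimate and interval

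*Protocol article*

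**What the plan says.** **Design.** The Allocation section of the protocol article describes central 1:1 randomisation, "stratified by center and the cause of the indication for ERCP". Indication has two levels: bile duct cannulation, or otherwise. With the eight hospitals named under Study settings, that makes 8 × 2 = 16 strata.

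**Primary analysis.** Under Statistical analysis: "For each allocation group, the percentage of PEP occurrences will be calculated", on the full analysis set, with exact Clopper-Pearson 95% intervals. Then Fisher's "exact test will be used to compare the groups", two-tailed at 5%, repeated in the per-protocol set for reference. The paragraph mentions neither stratification factor and no between-group measure. Odds ratios with 95% intervals come in the next paragraph, which opens by dividing patients into subgroups and ends with a forest plot.

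**Sample size.** Under Number of patients, the control risk is taken as 10% and the target is a halving to 5%. The calculation is given as "a two-sided α = 0.05 and a power of 0.8, 435 patients per study arm are required". Enrolment is set at 440 per group. On the effect size: "This absolute reduction in incidence is believed to be clinically relevant".

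**The concern.** Three parts of the plan do not fit together.

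1. The design treats centre and indication as important enough to balance on, and the primary comparison then drops both.
2. The sample size promises 80% power, but the formula that yields 435 is not the formula for the named test. Fisher's exact test on a 2×2 table is conservative, so its power should be lower.
3. The primary objective is to determine an effect on PEP incidence, and the trial is sized on an absolute reduction. Yet the primary paragraph offers two one-sample intervals and a p-value. A Clopper-Pearson interval describes one proportion, not a contrast.

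At stake are a few points of power that could be had at no cost, and a clear primary effect estimate with its uncertainty.

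**Working it through.** **Inputs.** Control risk 10%, ice water risk 5%, two-sided α = 0.05, power 0.80, 435 required and 440 planned per arm (Number of patients); 8 centres (Study settings) × 2 indications (Allocation); two-tailed Fisher test (Statistical analysis).

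**Step 1: reproduce 435.** The pooled-variance normal approximation without continuity correction is

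n = [z₀.₉₇₅ √(2p̄(1−p̄)) + z₀.₈₀ √(p₁(1−p₁) + p₂(1−p₂))]² / (p₁−p₂)², with p̄ = 0.075.

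- 2 × 0.075 × 0.925 = 0.13875, root 0.3725; × 1.960 = 0.7301
- 0.09 + 0.0475 = 0.1375, root 0.3708; × 0.8416 = 0.3121
- (0.7301 + 0.3121)² / 0.0025 = 434.4, rounded up to **435**

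The stated figure reproduces exactly. The continuity-corrected version, which lies closer to Fisher, gives 474.

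**Step 2: exact power and size of the planned test.** Sum the two binomial probabilities over all pairs of event counts for which the two-sided Fisher p is at most 0.05.

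| Per arm | Risks | Rejection probability |
|---|---|---|
| 435 | 10% vs 5% | 77.1% |
| 440 | 10% vs 5% | 77.7% |
| 474 | 10% vs 5% | 80.9% |
| 440 | 10% vs 10% | 3.8% |
| 440 | 7.5% vs 7.5% | 3.7% |
| 440 | 5% vs 5% | 3.5% |

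The power shortfall is 80 − 77.7 = 2.3 points. It needs no assumption about strata.

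**Step 3: where a gain would come from.** The same enumeration for a crude, uncorrected chi-square test at 440 per arm gives 81.6% power, with size 5.1% at a common risk of 10%. Dropping Fisher's conservatism alone is therefore worth 81.6 − 77.7 = 3.9 points.

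The CMH statistic without continuity correction is [Σ(aₖ − E(aₖ))]² / ΣVar(aₖ) over the 16 strata, with aₖ the ice water events in stratum k. It was simulated with assumed stratum sizes of 50 and 5 patients per arm in each centre (8 × 55 = 440), in 100,000 trials per scenario:

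| Assumed control risks across strata | CMH power | Crude chi-square power | Difference |
|---|---|---|---|
| All 10% | 81.1% | 81.4% | −0.3 |
| About 6-25% | 81.5% | 81.5% | 0.0 |
| About 4-37% | 82.3% | 81.9% | +0.4 |

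A separate, smaller simulation (20,000 trials; control risks all 10%, 5.6-24.6% and 3.1-32.2%) gave CMH power of 81.4%, 82.1% and 82.8%, with size about 4.8%. Its Monte Carlo standard error is about √(0.82 × 0.18 / 20,000) = 0.3 points, so the two runs agree.

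**Step 4: what the primary output would show at the design rates, 22/440 vs 44/440.**

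- As planned: 5.0% (3.2 to 7.5) and 10.0% (7.4 to 13.2), Fisher p = 0.007.
- Risk difference: SE = √(0.1375/440) = 0.0177; −5.0 points, 95% CI −8.5 to −1.5.
- Risk ratio: SE of the log = √(1/22 − 1/440 + 1/44 − 1/440) = 0.252; 0.50, 95% CI 0.30 to 0.82.
- Odds ratio: 0.47, 95% CI 0.28 to 0.80.

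The last three lines are unadjusted. None of them is named for the overall comparison.

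**The case against.** Stratifying for balance and then prespecifying a crude exact test is a defensible choice. It guarantees size control, does not depend on sparse centre-by-indication cells and needs no pooling rule. The two sections do not contradict each other. The strata themselves contribute almost nothing to power, and neither the share of pancreatic or combined indications nor the centre sizes are in the document. The article is also condensed: the effect measure accompanying a primary test is often left to an analysis plan, the odds-ratio sentence does mention PEP, and anyone given both percentages and denominators can compute the difference and its interval.

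Much of this stands, and it limits the point. A reader might infer that leaving out the strata makes the test invalid. It does not: size stays below 5%. A reader might also blame the low power on the missing strata. Step 3 shows that the cause is the exact test. Nor can one say that the effect will go unreported; the article does not restrict reporting to per-arm intervals. The overlap of those intervals in Step 4 is about 0.1 points (7.4 to 7.5%) and would stand beside a p-value of 0.007, so the risk of misreading is slight.

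Two things remain. The test is named with its sidedness and level, so its mismatch with the 80% power claim is in the stated text. And the article specifies a contrast with an interval for subgroups but not for the comparison on which the trial is sized.

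**Conclusion.** The point holds as a matter of efficiency and reporting, not of validity. The planned Fisher test has 77.7% power at 440 per arm (77.1% at 435) under the protocol's own rates, with size about 3.7-3.8% at common risks of 7.5-10%. These figures are exact and rest only on 10% versus 5%. A CMH test on the randomisation strata would bring power to about 81-82% at about 5% size. At most about 0.4 points of that gain come from stratification, and that part depends on assumed stratum sizes and risks. The case for the strata is therefore mainly that the analysis should follow the design and give one common effect estimate. The missing overall estimate is a gap in the primary paragraph that is easy to close.

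**What to change.** - Make the primary test a CMH test without continuity correction, stratified by centre and indication. State a rule for pooling sparse centres, fixed before unblinding.
- Name the Mantel-Haenszel risk difference with 95% CI as the primary effect estimate, and give the risk ratio with 95% CI beside it.
- Keep the per-arm Clopper-Pearson intervals as description and the crude Fisher test as a sensitivity analysis.
- If Fisher stays primary, restate its power as about 77-78% under Number of patients, and still add the risk difference with its interval.

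The cost is analysis wording only, since both factors are already used in the randomisation. The price of CMH is that it is asymptotic rather than exact and needs the pooling rule. Enrolment was ongoing when the article was written, so the change should be dated and made before any comparison of outcomes by arm.

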#### Secondary outcome measures

The secondary outcomes are as follows: (1) incidence of PEP in cases of difficult cannulation, (2) incidence of PEP by various ERCP procedures, (3) incidence of PEP by the presence of pancreatic duct cannulation and pancreatography, (4) incidence of PEP by cannulation time, (5) incidence of moderate and severe PEP, (6) incidence of PEP by high-risk factors for PEP, and (7) incidence of other complications.

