### Definitions

The severity of PEP is classified as follows, modifying Cotton criteria: mild disease, which requires 2–3 days of fasting; moderate disease, which requires 4–10 days of fasting; and severe disease, which requires 11 or more days of fasting[15]. In addition to the above, patients with necrosis or pseudocyst formation or those who underwent percutaneous drainage or surgery were defined to have severe disease[15].

Difficult cannulation is defined as contact with the papilla more than five times, cannulation time more than 5 min, and unintentional pancreatic duct cannulation more than two times [1]. Definition and severity of cholangitis prior to ERCP; in accordance with Tokyo Guidelines 2018[16]. ERCP trainee is defined as a physician with less than 200 cases of ERCP experience. The following factors have been identified as risk factors for PEP: (1) pre-cut sphincterotomy, (2) endoscopic pancreatic sphincterotomy, (3) endoscopic papillary balloon dilation, (4) difficult cannulation cases, (5) pancreatography, (6) female patients under 60 years old, (7) suspected SOD, (8) history of recurrent pancreatitis, and (9) history of PEP[1].

Regarding other ERCP comorbidities, hemorrhage is defined as hematemesis or a drop in hemoglobin concentration of > 2 g/dL and perforation as the presence of air or intestinal contents beyond the intestinal tract[17]. Other comorbidities and their severity follow the ASGE guidelines[17].

The ice water used in this study is defined as 250 mL of chilled water in a refrigerator with ten ice cubes made with an ice machine.

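### The stated subgroup method, Fisher's test within each subgroup with no arm-by-factor test named, cannot show whether the effect of ice water differs between subgroups

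*Protocol article*

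**What the plan says.** The Statistical analysis section of the protocol article sets out the subgroup method in some detail:

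- The arms are compared inside each subgroup: "After dividing the patients into subgroups according to background factors, comparisons between the groups will be made".
- Binary outcomes get an odds ratio with 95% CI and a Fisher's exact test, and the results go on a forest plot.
- For continuous factors: "When the background factor is a continuous variable, subgroups will be created based on the median value".
- The only significance level in the article is given with the main comparison: "The test will be two-tailed with a significance level of 5" percent. No other level is given for subgroups.

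No test of arm by factor is named. Under Secondary outcome measures, items 1, 2, 3, 4 and 6 of the seven are pancreatitis by subgroup, for example "incidence of PEP by cannulation time". The only sizing, under Number of patients, is for the overall comparison.

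**The concern.** A test within a subgroup asks whether there is evidence of an effect in those patients. A forest plot across subgroups is normally read for something else, namely whether the effect differs between them. Separate p-values do not answer that. When each subgroup has too few patients for reliable detection, chance alone will often put one p-value below 0.05 and its neighbour above it, even if the true effect is identical in both.

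What is at stake is the reading of the secondary results. A uniform benefit could be reported as confined to one kind of patient or procedure.

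**Working it through.** **Inputs from the article.** Number of patients gives the control rate ("Assuming a baseline PEP risk of 10% in normal native papilla"), the power ("and a power of 0.8"), two-sided α = 0.05, and the target of 440 per arm. Allocation is 1:1. An even split of one factor therefore leaves about 220 per arm in each half.

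**Reproducing the plan's figure.** The article says "435 patients per study arm are required to detect a 50% reduction in the incidence of PEP to 5" percent. With pooled variance and mean rate 0.075:

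n = [1.960·√(2·0.075·0.925) + 0.842·√(0.10·0.90 + 0.05·0.95)]² / 0.05² = 434.4, rounded up to 435.

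This matches.

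**Same effect in both halves (10% vs 5%).** Summing the two binomial distributions over every table that two-sided Fisher rejects at 5%, with 220 per arm, gives power p = 0.450 per half. The halves are independent, so:

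| Pattern | Formula | Probability |
|---|---|---|
| Both significant | p² | 0.202 |
| Exactly one significant | 2p(1 − p) | 0.495 |
| Neither significant | (1 − p)² | 0.303 |

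Uneven splits give more discordance: 0.51 for 40/60, 0.55 for 30/70 and 0.61 for 20/80. In simulated trials where the overall Fisher test was significant, about 59% of evenly split factors had exactly one significant half.

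**Interaction test, same scenario.** A Wald test on the difference in log odds ratios between the halves rejected in about 4-5% of simulated factors.

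**No effect (10% vs 10%).** Fisher's actual size at 220 per arm is 0.0353.

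- One factor, at least one significant half: 1 − (1 − 0.0353)² = 0.069, against 0.05 for one interaction test.
- Ten independent factors (an assumed number): 1 − (1 − 0.0353)²⁰ = 0.51, against 1 − 0.95¹⁰ = 0.40 for ten interaction tests.

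**Power of the interaction test.** Suppose only one half benefits (10% vs 5%) and the other does not (10% vs 10%).

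- Difference in log odds ratios: ln[(0.05/0.95)/(0.10/0.90)] = −0.747.
- Variance from expected counts: 1/11 + 1/209 + 3·(1/22 + 1/198) = 0.247, so SE = 0.497.
- 0.747/0.497 = 1.50, and power is Φ(1.50 − 1.96) ≈ 0.32. Simulation gives 0.31.

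**Events available for modelling.** 440·0.10 + 440·0.05 = 44 + 22 = 66. A model with arm, factor, interaction, indication stratum and seven center terms has 11 parameters, or 66/11 = 6 events each.

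**The case against.** **The article is a condensed text.** An interaction test or an exploratory label may stand in a full protocol or analysis plan that is not shown. That is fair, and the absence alone would be no finding. But the article does not leave the method open. It fixes the test, the cut rule and the display, and the chosen test does not answer the subgroup question.

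**No decision rule is stated.** The article never says that benefit will be claimed or denied in a subgroup on these p-values, and odds ratios with intervals on a forest plot already help a careful reader. This stands. A reader might infer that the plan will produce false subgroup claims, but the text supports only a marked risk of misreading.

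**A null trial gains little.** This also stands. The like-for-like contrasts are 7% against 5% per factor, or 51% against 40% over ten assumed independent factors. The article does not give the number of factors, and correlation between them would lower both totals.

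**The median cut.** A reader might infer that it clashes with the clinical thresholds under Definitions. It does not. The 5-minute limit is one part of the definition of difficult cannulation, and "female patients under 60 years old" is a combined sex-and-age risk factor. Neither is offered as a subgroup cut for cannulation time or for age in all patients. Nor does a median cut inflate type I error, since it is set without regard to outcome. Its only fault is lost information.

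**Interaction tests are weak, and the model can be overloaded.** Both are true, and both limit the remedy.

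**Conclusion.** The point holds as an inexpensive improvement to the secondary analyses. Under the plan's own rates and a uniform effect, an even split shows significance in exactly one half in about 49% of trials, where an interaction test would flag about 4-5%. That result needs only the 10% and 5% rates, about 220 per arm in each half, and the 5% level carried over to subgroups. It does not depend on how many factors are examined.

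The weight of the point comes from the five subgroup-type secondary outcomes. It is an inference that the background-factor method also serves those measured during the procedure, such as cannulation time, but the article describes no other subgroup method. The primary comparison, its sample size and its conclusion are unaffected.

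**What to change.** In the Statistical analysis section:

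1. For each factor, show subgroup odds ratios with 95% CI on the forest plot, together with one arm-by-factor interaction p-value from a logistic model with arm, factor and their interaction. With about 66 events expected, leave out full center adjustment.
2. Drop the within-subgroup Fisher p-values.
3. Label the subgroup results exploratory.
4. As a minor point, keep continuous factors continuous in the interaction model. A split can still be used to display them.

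The cost is a few sentences and a few lines of code, with no extra patients or data. The drawback is low power, about 31% if only one half benefits, so the text should also say that a non-significant interaction does not prove a uniform effect. The change does not control multiplicity across factors, which is a further reason for the exploratory label.
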